### Usual Care (Control)

Usual care refers to clinical GDM care processes currently in practice at the participating hospitals, and this will be the control group. In line with recommended best practice [29,30] diagnostic screening for GDM occurs at 24 to 28 weeks gestation for women with no known history of diabetes or earlier for those considered high risk for GDM. Following diagnosis through to end of pregnancy, ongoing care is provided via a multidisciplinary team of endocrinologists, dietitians, and CDE-RNs. The role of the team is in addition to obstetric care.

From an endocrinology perspective, care involves an initial group counseling and education with a CDE-RN and dietitian covering aspects of GDM self-management. The CDE-RNs provide the pregnant women with free BGL meters from an approved supplier. The meters are individual use and the women purchase their own consumables (ie, test strips and lancing devices). Treatment targets are ≤5.0 mmol/L for preprandial BGL and ≤6.7 mmol/L for 2-hour postprandial BGLs. Insulin is initiated or titrated if BGLs are above target over three successive days. Ongoing face-to-face appointments are scheduled with members of the team as needed until delivery. Appointments generally occur every one to two weeks as determined by the clinicians. Patients on insulin have more frequent reviews especially in the early stages of insulin initiation. Self-management involves keeping a daily paper diary record of GDM self-monitoring data (1 preprandial and 3 postprandial BGLs, insulin dosing, symptoms, and dietary information). The diaries are reviewed by the clinicians at each outpatient clinic. The women also have the option to call the CDE-RNs out of scheduled appointments if BGLs are outside target.

### Telemedicine (Intervention)

The intervention is telemedicine as an adjunct to usual care. The main distinction to usual care is GDM self-monitoring data is shared via a telemedicine system in lieu of paper diaries. The intervention uses a Web-based portal, Online Health Portfolio (OHP) [31], for data sharing and communication between patients and clinicians and is premised upon (1) women with GDM undertaking regular GDM self-monitoring and entering data; (2) timely availability of data to clinicians via the Web-based OHP, hence timely response to the women’s GDM care needs informed by the available data; and (3) upon carrying out advice and feedback the women will better manage GDM and require less frequent appointments. Currently there is no empirical evidence for OHP, and it was chosen for this study on pragmatic reasons and anecdotal accounts of independent endocrinologists who used it in their practice.

Online Health Portfolio is a secure Web-based patient-controlled personal health record that is accessed securely through an Internet browser on a personal computer, smartphone or tablet. It is a proprietary system developed and owned by a vendor who is independent of the study. It uses 256-bit data encryption and 5-minutes inactivity time logout. Besides data entry and preview, the users can have graphical visualization of summary data and trends filtered by pre- or postprandial meal type or time, set up automatic reminders on the internal calendar, and set trigger levels for BGL alerts. Reminders may be forwarded to the patient’s smartphone as a short message service (SMS) text. There is an internal messaging feature within OHP to enable 2-way messaging of free text between clinicians and patients. Clinicians also have the option to send an SMS text to the patient’s smartphone from OHP. Participating patients use their own Internet-connected devices while clinicians use their usual hospital-provided Internet-connected computers. Username and password access to OHP is independent of all other hospital applications and systems. While patients are at liberty to access OHP at any time, clinicians interact with OHP during the course of normal work hours (8:00 AM to 4:30 PM), Monday through Friday. Multimedia Appendix 1 and Multimedia Appendix 2 show of some screenshots of the OHP.

**Figure 2 figure2:**
[figure not shown]
Diary view format introduced after modifications to enhance usability of OHP.

Upon enrollment, patient participants undergo individual semistructured 30 to 45 minutes induction by the lead researcher or research assistants.

The induction is hands-on and covers the initial set-up with participants practicing all the tasks they are expected to perform independently from then on. Induction covers signing up, logging on, navigating through the OHP Web portal, data entry, messaging, and reviewing data trend/summary graphs. All data entry is practiced using the previous day’s data. Performing BGL self-monitoring, administering insulin, and following dietary advice are part of routine diabetes education and counseling provided by a multidisciplinary endocrinology care team as described under usual care. Participants are also instructed on how to share this health information with the GDM clinicians for the purpose of providing clinical care and with the project lead investigator for research data collection and data management purposes. When required and in order to improve study data collection, the lead researcher may set up automatic reminders on OHP to send reminders every second day to prompt the noncomplying patient to enter data. Activating or setting up automated reminders is not routine but it is targeted for those who fail to perform data entry according to expectations. This avoids inundating those who are compliant with unnecessary reminders.

Participants are asked to enter their GDM self-monitoring data onto OHP daily or every other day in order to minimize backlogs and associated data entry errors. Maintaining a paper diary is optional. Automated alerts about new data entries are sent to the clinicians via email prompting the clinicians to log in under their credentials to review the patient data. When required and depending on the reviewed data or patient queries, clinicians provide feedback to the patient via the messaging service about any necessary alterations to treatment (eg, insulin titrations, changes to diet). The CDE-RNs act as the gatekeepers to interact with the telemedicine system and to consult or liaise with other GDM service team members. Patients can also email or print reports for other interested parties who do not have direct access to the Web-based shared data.

Induction for clinicians involved in providing care was conducted by the lead researcher. It consisted of setting up log-on credentials, using and navigating through the OHP webpage, setting up alerts, reviewing patient data, and messaging. The induction included both demonstration and hands-on practice in group setting.

Tasks expected of clinicians are to review patient data at their convenience, fitting in with their other routine clinical commitments through the day during weekdays. At the minimum, data are reviewed every 1 to 2 days during the week. Clinical decision making and advice in relation to ongoing management of GDM is at the discretion of the clinicians in accordance with existing clinical protocols without interference from the researchers. The same applies to scheduling of clinic appointments. Clinicians may also remind a patient when no data have been entered.

For research data collection, participant engagement, and/or troubleshooting purposes, the lead researcher periodically contacts participants via the OHP messaging feature or telephone and extracts all data from OHP to collate in a secure MS Access study database. The lead researcher is the primary contact for basic technical support queries, escalating any queries that cannot be resolved to the OHP vendor.

### Sample Size

As an exploratory RCT, a stringent sample size calculation was deemed to be less critical for the TeleGDM trial. Therefore sample size has been set at 100 participants. This determination was largely pragmatic, based on resources, time constraints, the balance of probability for detecting a statistically significant difference in the primary outcome and a reasonable power for secondary outcomes. Estimations based on a finding of 44% fewer clinic visits among those receiving telemedicine versus controls [32] indicated a required sample size of 42 with a power of 0.9 for a similar outcome. Thus if the primary outcome in our study were to be less than the latter cited study, or there was 30% attrition, our set target sample offers good prospects for detecting a difference in the primary outcome.

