Specifically in GDM, telemedicine interventions compared to control/usual care may reduce service utilization such as face-to-face clinic visits (4.25 [standard deviation or SD 0.93] vs 6.22 [SD 1.48], respectively; *P*=.002) and unscheduled visits (0.50 [SD 0.73] vs 2.89 [SD 1.05], respectively; *P*<.001) [12], while achieving similar outcomes (with trends in favor of telemedicine) for glycemic control, birth weight, incidence of macrosomia [11,12,17,18] and diabetes self-efficacy [12,17-19]. The main limitations of studies of telemedicine in GDM that we identified in our systematic review of the literature [11] are that there are very few randomized controlled trials (RCT) and sample sizes tend to be small. None of the trials included in our review evaluated costs, perhaps due to the lack of an agreed standardized evaluation framework for telehealth interventions. We also identified other methodological limitations such as shorter interventions and the heterogeneous nature of the outcomes and telehealth interventions used [10,20-22]. Interventions were perhaps too short to have significant measurable impacts; outcome measures varied across studies, posing challenges to conducting effects through pooled data analysis, and the interventions varied considerably, ranging from telephone support and videoconferencing to text messaging [10,20-22], making comparison of studies and generalizability difficult.

Our innovative study, the Telemedicine for Gestational Diabetes Mellitus (TeleGDM) trial, uses a Web-based approach to augment the management of women with insulin-treated GDM. Our aim is to explore the effects of telemedicine on health system performances including patient utilization of outpatient clinical care, maternal and fetal clinical health outcomes, and patient and clinician satisfaction and acceptance with respect to the intervention technology. In addition, a cost comparison between the two arms of the trial will be performed to determine if there are any provider cost savings that might be associated with changes in outpatient clinic attendance.

We hypothesize that with timely access to patient GDM self-monitoring data, health service utilization would be decreased without compromising maternal and fetal outcomes with an associated provider cost saving, greater satisfaction with the telemedicine, and a positive user experience.

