### Recruitment and Randomization

The women with GDM regularly attend outpatient GDM clinics at the hospitals. It is at these weekly clinics that prospective participants are recruited face-to-face. Clinicians identify potentially eligible patients, give them a study brochure and/or seek permission for referral to the lead researcher or study research assistants. Following referral, participants are approached for face-to-face screening, detailed briefing, consent, randomization, and completion of baseline questionnaires. A 1:1 randomization schedule was generated in STATA 11.0 (StataCorp LP) by an independent statistician. The lead researcher and RAs have no involvement in routine care of the patients.

Some ethnic groups (Indian, Asian, Arabic/Middle Eastern, Pacific Islander, Aboriginal, and African) are considered high risk for GDM [27]. Previous GDM and use of insulin in past pregnancies are also considered high risk factors for GDM. Therefore randomization was stratified according the level of risk (high or low). Stratification avoids group allocation imbalances on factors that have significant influence on prognosis, avoids type 1 error, and improves study power for small trials [28]. Group assignments are concealed in two sets of opaque envelopes; the first set is the randomization schedule for the low risk subgroup and the second for the high risk GDM subgroup. Following consent, the envelopes are consecutively opened for assignment by the recruiter. Clinicians are not blinded to group allocations because they need data from the intervention for clinical care.

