The primary outcome of the quantitative exploratory RCT component of the study is service utilization. Maternal and fetal outcomes, satisfaction, and costs are secondary outcomes. In particular, one of the limitations of studies in our systematic review [11] was the lack of cost evaluation, however basic. Considering that studies appear to show virtually similar clinical outcomes between telemedicine and usual care/control [12,17-19], a form of cost comparison becomes important. There are several methods for undertaking health economic evaluation, one of which is cost minimization. This type of health economic evaluation is defined as “. . . evaluation method to use when the case for an intervention has been established and the programmes or procedures under consideration are expected to have the same, or similar, outcomes. In these circumstances, attention may focus on the cost side of the equation to identify the least costly option” [39]. At the time of this protocol study, patients not covered by the Australian Medicare paid AUD $280 for each face-to-face consultation with a clinician for GDM care at the centers in this study. Because diabetes education, endocrinology, and dietetics are the key outpatient specialties involved directly in GDM management and therefore targeted for influence by the TeleGDM intervention, the AUD $280 cost rate will be assigned to these for service provided to patients between study entry and study exit. Study participant outpatient consultations data covering service access between commencement of recruitment and end of data collection for computation of provider costs will be sourced from the hospital data management unit. While clinicians provide service over the phone, which is a cost to the hospital, patients are not billed and hence this cost will not be included. Furthermore, implementing the intervention required existing equipment and infrastructure for the brief induction. Costs for these were considered negligible and therefore were not taken into consideration. Also Australian public hospitals by their nature are nonprofitmaking entities. Where fees are charged these are normally break-even and include overheads. Besides the AUD $85 per patient subscription there is no separate license fee for OHP.

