### Data Preparation and Analysis

Quantitative data analysis will be performed using Stata/IC 13.1 (StataCorp LP) with an intention to treat analysis. Missing data for the primary outcome is expected to be minimal as all patient appointments and outcomes are recorded. For the DES and CSQ-8 losses to follow-up will employ last observation carried forward for missing values. Since case BGL data is serial and expected to be nonlinear, case mean of nearby data points imputation will be used for missing data.

Summary univariate statistics will be used to describe the study populations and compare study groups at baseline. Categorical variables will be summarized as raw numbers and percentages and between groups comparisons will utilize chi-square statistics. Multivariate statistical analysis will be performed to compare the groups on primary and secondary outcomes. In addition, survival analysis will be performed to explore time to reach glycemic stability. Statistics will be reported with standard deviations or 95% confidence intervals as appropriate. Statistical significance will be indicated by *P*<.05.

Patient and clinician interviews will undergo thematic analysis supported by NVivo 11 (QSR International). The interview transcripts will be analyzed separately for each participant group using an inductive approach to identify and/or infer themes and codes from the transcripts. Further themes will be classified according to the dimensions of telehealth evaluation framework [41].

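### The claim of reasonable power for secondary outcomes fails for the binary maternal and fetal outcomes, so a non-significant difference could not support the no-worse half of the hypothesis

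*Protocol article*

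**What the plan says.** All references are to the protocol article.

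- **Sample Size.** The trial is exploratory and its size largely pragmatic: "Therefore sample size has been set at 100 participants". One of the stated grounds is "a reasonable power for secondary outcomes". The only calculation described is for the primary outcome, service utilization. It starts from "44% fewer clinic visits among those receiving telemedicine versus controls" and arrives at 42 with power 0.9. No secondary outcome, effect size, standard deviation or event rate is given.
- **Introduction.** The hypothesis is that "health service utilization would be decreased without compromising maternal and fetal outcomes". The first half is a superiority claim and the second half is a no-worse claim.
- **Table 1.** Secondary outcomes include large for gestational age, neonatal admission to special care nursery and type of delivery. They also include outcomes on a score or time scale, such as DES-SF, CSQ-8 and days to glucose stabilization.
- **Data Preparation and Analysis.** Groups are to be compared on primary and secondary outcomes. "Statistical significance will be indicated by" P<.05. Standard deviations or 95% confidence intervals will be given where appropriate. No margin is stated for the no-worse half.
- **Data and Outcomes.** Cost minimization is introduced through a definition that calls it an "evaluation method to use when the case for an intervention has been established" and outcomes are expected to be the same or similar. The section on the intervention says: "Currently there is no empirical evidence for OHP".

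**The concern.** A stated ground for the sample size is a property that the trial does not have for the clinical outcomes most relevant to mother and baby. At 50 per arm a non-significant comparison is the likely result even if one of these outcomes is materially worse or better. The hypothesis nevertheless includes no worsening of these outcomes, and the only decision criterion is a significance threshold for a difference. A reader told that power was reasonable would be inclined to take a null result as reassurance. The cost comparison is set beside this: a cost saving is easy to endorse if clinical outcomes are taken to be the same, and the trial will be able to say little about whether they are.

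**Working it through.** **The plan's own figure.** There is no figure for secondary-outcome power to reproduce. The one figure given, 42 for the primary outcome, cannot be reproduced because no control mean or standard deviation is stated, nor whether 42 is total or per arm. It is arithmetically possible. If total (21 per arm), it implies a standardized difference of (1.960 + 1.282) × √(2/21) = 1.00; if per arm, (1.960 + 1.282) × √(2/42) = 0.71. It is not shown to be wrong, and nothing below depends on it.

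**Inputs.**
- 100 women (Sample Size), allocated 1:1 (Recruitment and Randomization: "A 1:1 randomization schedule was generated in STATA 11.0"), so n = 50 per arm.
- Significance level 0.05 (Data Preparation and Analysis). Two-sided is my assumption.
- Control event rates are not in the document. I assume 10% to 40% for any binary outcome, with type of delivery taken as cesarean or not.
- Sensitivity case: the 30% attrition mentioned under Sample Size leaves 100 × 0.7 = 70, or 35 per arm.

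**Power for a binary outcome.** With control rate p1, comparison rate p2 and mean rate p̄, power = Φ[(|p1 − p2| − 1.96·s0)/s1], where s0 = √(2p̄(1 − p̄)/n) and s1 = √((p1(1 − p1) + p2(1 − p2))/n).

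Example, 20% against 10% with n = 50: p̄ = 0.15, s0 = √(2 × 0.15 × 0.85/50) = 0.0714, s1 = √((0.16 + 0.09)/50) = 0.0707. Power = Φ[(0.10 − 0.140)/0.0707] = Φ(−0.565) = 0.286.

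**Precision.** Half-width of the 95% interval for a risk difference with equal rates p = 1.96 × √(2p(1 − p)/n). At p = 0.20 and n = 50: 1.96 × √(0.32/50) = 0.157.

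| Assumed control rate | Power, halving, 50/arm | Power, halving, 35/arm | Power, 10-point rise, 50/arm | Half-width, 50/arm | Half-width, 35/arm |
|---|---|---|---|---|---|
| 10% | 15.5% | 12% | 29% | 11.8 points | 14.1 points |
| 15% | 22% | 17% | 24% | 14.0 | 16.7 |
| 20% | 29% | 21% | 21% | 15.7 | 18.7 |
| 30% | 43% | 32% | 18% | 18.0 | 21.5 |
| 40% | 59% | 45% | 17% | 19.2 | 23.0 |

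An increase detectable with 80% power at 50 per arm would have to be from 10% to 33%, 20% to 46%, or 30% to 58%.

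**Continuous outcomes.** The standardized difference detectable with 80% power is (1.960 + 0.842) × √(2/50) = 0.56 by the normal approximation and 0.57 by the t distribution. With 35 per arm it is 0.67 or 0.68. At a standardized difference of 0.5, normal-approximation power is 71% with 50 per arm and 55% with 35.

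**What a null result would exclude.** Suppose 18 of 50 women against 10 of 50 have an event (36% and 20%). The difference is 16 points with standard error √(0.36 × 0.64/50 + 0.20 × 0.80/50) = 0.0884, so the 95% interval is 16 ± 17.3, about −1 to +33 points. The chi-square P value (no continuity correction) is .07. By the stated threshold this is not significant, yet an excess of up to 33 points remains possible. Even identical observed rates of 20% would leave an excess of about 16 points not excluded.

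**Size a no-worse test would need.** For an illustrative 10-point margin at 20%, one-sided 0.025, 80% power and true difference zero: n = (1.960 + 0.842)² × 2 × 0.20 × 0.80/0.10² = 251.2, so 252 per arm. Over rates of 10% to 40% the figure is 142 to 377 per arm. The margin is an assumption; the document gives none.

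**The case against.** Several points on the other side stand.

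- The power phrase covers all secondary outcomes. Many are continuous or time-to-event, and for those a detectable difference of about 0.57 standard deviations can fairly be called reasonable. It would be wrong to say that the trial has no useful power for any secondary outcome. Very large binary differences are also detectable: 30% against 60% has 87% power with 50 per arm.
- A reader might infer that P>.05 will be taken to mean outcomes were not compromised. The document nowhere says so. The no-worse statement is a hypothesis, the Conclusions say only that telemedicine may achieve it, and the trial is repeatedly called exploratory. No claim of equivalence is made.
- Confidence intervals are already foreseen, so the difference test is not the only planned reporting.
- A reader might also infer that the cost analysis depends on this trial's own non-significant results. It does not. The section takes similarity from earlier studies, the quoted definition asks only for expected similarity, and the protocol's own label is a form of cost comparison.
- The 35-per-arm figures may be too pessimistic for delivery outcomes, which come from medical records. The attrition figure is raised as a possibility in discussing the primary outcome.
- A condensed article need not show secondary power calculations, so their absence is not the point.

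What remains is that the article makes an affirmative claim, and the claim is untrue for the binary clinical outcomes even with all 100 women analyzed. The exploratory label is a reason to drop the claim. Planning intervals as appropriate does not settle how a null result on a no-worse hypothesis will be read.

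**Conclusion.** The point holds in limited form. For large for gestational age, special care nursery admission and type of delivery, the stated reasonable power does not exist: about 15% to 59% for a halving and 17% to 29% for a 10-point increase, with intervals of about ±12 to ±19 points. This rests on 50 per arm, two-sided 0.05, and assumed control rates of 10% to 40%. No halving within that range reaches 60% power. For continuous secondary outcomes the phrase is arguable. The no-worse half of the hypothesis has no margin, so a non-significant difference could not support it.

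The cost issue is a smaller wording matter. The definition quoted for cost minimization presupposes an established case, while the protocol says that the portal has no empirical evidence. Similarity is therefore an assumption brought in from studies of other systems.

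The primary outcome, its analysis and the sample size are unaffected. This should be corrected, but it is not a critical defect.

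**What to change.** 1. In Sample Size, delete the phrase on secondary power, or restrict it to named continuous outcomes and state the detectable effect (80% power at a standardized difference of about 0.57 with 50 per arm).
2. Add the achievable precision for binary clinical outcomes: about ±12 to ±19 percentage points at assumed event rates of 10% to 40%.
3. In Data Preparation and Analysis, commit to reporting each maternal and fetal outcome as a between-group difference with its 95% confidence interval. State that a non-significant difference will not be interpreted as outcomes not being compromised, and that the confidence limit in the direction of harm will be reported as the largest excess not excluded.
4. In Data and Outcomes, describe the cost analysis as a cost comparison conditional on assumed similar clinical outcomes, and present it beside the clinical estimates and their intervals.

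The cost is wording only. No extra participants, data or analyses of a new kind are needed. The downside is a less favourable stated claim about what the trial can show on clinical outcomes.
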